## Abstract

**Background:**

Allogeneic stem cell transplantation (allo-HCT) is associated with high treatment-related mortality and innumerable physical and psychosocial complications and side-effects, such as high fatigue levels, loss of physical performance, infections, graft-versus-host disease (GvHD) and distress. This leads to a reduced quality of life, not only during and after transplantation, but also in the long term. Exercise interventions have been shown to be beneficial in allo-HCT patients. However, to date, no study has focused on long-term effects and survival. Previous exercise studies used ‘usual care’ control groups, leaving it unclear to what extent the observed effects are based on the physical effects of exercise itself, or rather on psychosocial factors such as personal attention. Furthermore, effects of exercise on and severity of GvHD have not been examined so far. We therefore aim to investigate the effects and biological mechanisms of exercise on side-effects, complications and survival in allo-HCT patients during and after transplantation.

**Methods/design:**

The PETRA study is a randomized, controlled intervention trial investigating the effects of a yearlong partly supervised mixed exercise intervention (endurance and resistance exercises, 3–5 times per week) in 256 patients during and after allogeneic stem cell transplantation. Patients in the control group perform progressive muscle relaxation training (Jacobsen method) with the same frequency. Main inclusion criterion is planned allo-HCT. Main exclusion criteria are increased fracture risk, no walking capability or severe cardiorespiratory problems. Primary endpoint is overall survival after two years; secondary endpoints are non-relapse mortality, median survival, patient reported outcomes including cancer related fatigue and quality of life, physical performance, body composition, haematological/immunological reconstitution, inflammatory parameters, severity of complications and side-effects (e.g. GvHD and infections), and cognitive capacity.

**Discussion:**

The PETRA study will contribute to a better understanding of the physiological and psychological effects of exercise training and their biological mechanisms in cancer patients after allo-HCT. The ultimate goal is the implementation of optimized intervention programs to reduce side-effects and improve quality of life and potentially prognosis after allogeneic stem cell transplantation.

**Trial registration:**

ClinicalTrials.gov Identifier: NCT01374399.

## Background

Allogeneic stem cell transplantation (allo-HCT) is the only curative medical treatment option for patients with haematological malignancies in high-risk situations e.g. acute leukaemia. However, patients suffer from numerous treatment related side-effects and complications, and the transplant-related mortality is high [1]. Exercise constitutes a potentially promising intervention approach for this patient group. Over the last years, several clinical trials have contributed to the growing body of evidence showing the beneficial effects of exercise in cancer patients [2–5], and some general exercise recommendations for cancer patients have already been published [6] also in the field of allo-HCT [7].

Our group has reviewed exercise intervention studies in the context of stem cell transplantation and illustrated that exercise interventions at different time points during and after HCT might significantly improve physical performance, quality of life, symptom control and fatigue [7]. Since publication of this review, 6 new randomized controlled trials (RCTs) have been published supporting the findings [8–13]. These studies were included in a recent review and meta-analysis by Persoon et al. [14] and the authors found that exercise significantly improved cardiorespiratory fitness, lower extremity muscle strength and fatigue and had also a small effect on upper extremity muscle strength, quality of life (QoL), physical, emotional and cognitive function. The researcher concluded that more high-quality studies were needed [14]. However, it is still not possible to give patients clear advice regarding the best type, intensity, start and duration of an exercise program.

Prior to allo-HCT, patients’ physical performance is already affected due to the disease itself and/or previous treatment [15, 16]. Furthermore, emerging evidence indicates that cancer patients have considerably impaired cardiorespiratory fitness as a result of the toxic effects of anticancer therapy or as a consequence of the disease (for example cachexia, deconditioning, anaemia) [17]. Thus, physical activity levels have been described as generally low in a group of haematological cancer survivors [18]. Furthermore, one study compared the quality of life of 662 HCT survivors with age- and sex-matched healthy controls and observed poorer general health, physical function, well-being, depression, cognitive function, and fatigue in HCT survivors [19]. A major complication after allo-HCT is graft-versus-host disease (GvHD). GvHD is the leading cause of morbidity and high transplant-related mortality. It is characterized by a reaction of donor T-cells against patient tissues e.g. mucosa or skin [1, 20]. Moreover, chronic GvHD is associated with a lower physical performance and functional capacity [21]. A recent review shows that patients after HCT are likely to have long-term difficulties with physical functioning, problems with fatigue, distress and a deteriorated psychological well-being [22]. Furthermore, patients after allo-HCT are at increased risks of cardiovascular events and pulmonary complications [23, 24].

Moreover, fatigue is a frequently reported adverse side-effect in cancer patients [25]. One study described the fatigue experience in allo-HCT patients during the first 100 days. In this observation, 68 % reported fatigue at the day of transplantation, 90 % at day 30 and 81 % at day 100 after allo-HCT [26]. A Cochrane review and an American College of Sports Medicine (ACSM) roundtable concluded that exercise may be an effective treatment against fatigue [2, 6]. Our recently published RCT supports these finding by demonstrating positive effects of exercise during and after allo-HCT on fatigue [13]. Mechanisms underlying the positive effect of exercise on fatigue are not fully elucidated, current models favor physiological and biological effects, for example enhanced physical performance, reduced inflammation, and less distress [27, 28].

A recent Cochrane review aimed to evaluate the effects of aerobic exercise in haematological malignancies. Exercise improved quality of life, especially physical functioning, depression and fatigue. The authors emphasised that none of the included studies investigated effects on survival. They concluded that trials with overall survival as primary endpoint are needed [29]. So far, the evidence regarding a possible influence of exercise on survival after cancer diagnosis is limited. A recent review by Ballard-Barbash et al. [30] found consistent evidence from 27 observational studies, that physical activity is associated with reduced all-cause, breast-cancer and colon-cancer specific mortality, but evidence regarding other cancers is currently insufficient [30]. Studies suggest that cardio-respiratory fitness may be a robust predictor of prognosis in non-small lung cancer patients and metastatic breast cancer [17, 31]. Courneya et al. [32] presented for the first time data from a RCT in 242 breast cancer patients, and found a non-significant trend for a better outcome (overall survival and disease-free survival) in the exercise group [32]. In addition, a small cohort study with 22 patients showed that patients with low cardiorespiratory fitness before allo-HCT had a higher risk of mortality after allo-HCT [33], furthermore, in a prospective cohort study in allo-HCT patients, the Karnofsky Performance Score (KPS) was an independent predictor of survival, and KPS <90 % was a predictor of non-relapse mortality (NRM) [34].

Data from our RCT in allo-HCT patients [13] also suggest a potential effect of exercise on survival. We observed a significantly reduced two-year total mortality (TM) for the experimental group (12 vs. 28 %, *p* = .034) after inpatient period. The effect was controlled for major confounding factors (Gratwohl Score, KPS, conditioning regime, gender, and fitness prior transplantation). Similar results were observed for non-relapse mortality (4 vs. 13 %, *p* = .017) when controlled for potential confounders. When we included the inpatient period, the risk reductions were similar but not significantly different. Interestingly, fitness at baseline was protective against NRM (*p* > .001). These results are encouraging, however, a major limitation of this study is that this was a post-hoc analysis and the study was not powered for the primary endpoint survival [35].

In consequence of the above mentioned findings, we currently perform an RCT to investigate the effects and biological mechanisms of a partly supervised yearlong exercise training on prognosis, complications, side-effects and biomarkers in patients during and after allo-HCT. To determine the specific effect of the exercise intervention itself beyond potential psychosocial effects, patients in the control group receive a comparable training schedule but with muscle relaxation according to the Jacobsen method, and the same personal attention as the exercise group.

## Methods/design

### Study design

The PETRA study (acronym for Physical Exercise Training versus Relaxation in Allogeneic stem cell transplantation) is a 12-month prospective, randomized, controlled clinical intervention trial in patients during and after allogeneic stem cell transplantation. Patients have to provide written informed consent prior to participation in the study. After baseline assessments, participants are randomized to a mixed type exercise program (resistance and endurance exercises) or a relaxation program over a period of one year. Both interventions are administered partly supervised. Endpoints are assessed before admission to hospital (baseline, t0), at the day of discharge (t1), day 100 after transplantation (t2), and day 180, 270 and 365 post transplantation (t3, t4, t5). Follow-up measurement will be 720 days after transplantation. [see Fig. 1].

**Fig. 1 Fig1:**
[figure not shown]
CONSORT: Study Flow of the PETRA study

The PETRA study has been approved by the ethic committees of the Ethic Committee II of the University of Mannheim (number 2009–349 N-MA) and Heidelberg University (number S-021/2011) and is registered at ClinicalTrials.gov (NCT01374399).

### Objectives

The primary objective of PETRA is to determine the effect of exercise on 2-year overall- survival after allo-HCT.

Secondary objectives are to estimate the effect of exercise on 2-year non-relapse mortality, median survival, fatigue, quality of life, physical fitness, including muscle strength, cardio-respiratory fitness, and body composition as well as on cognitive function. The effects of exercise on immunologic and inflammatory parameters and factors relevant for cancer prognosis and GvHD will be investigated and compared to the progressive muscle relaxation group. Finally, the sustainability of the effects will be assessed 720 days after allo-HCT.

### Outcome measures

The outcome measures used in the PETRA study are summarized in Table 1.

**Table 1 Tab1:** Assessments and instruments used in the PETRA study

Outcomes	Instrument	t0	t1	t2	t3	t4	t5	t6
Primary endpoint								
Overall 2-year survival	Medical log (ongoing assessment)							
Secondary endpoints								
2-year non-relapse mortality, median (disease-free) survival	Medical log (ongoing assessment)							
Quality of life	EORTC QLQ30 / HDC-29 module	X	X	X	X	X	X	X
Fatigue	Multidimensional Fatigue Inventory (MFI)	X	X	X	X	X	X	X
Muscle strength	Isometric and isokinetic strength of representative muscle groups for upper and lower extremity measured at the IsoMed2000®	X			X		X	X
	Hand-Held-Dynamometer (isometric)	X	X	X	X	X	X	X
Cardiorespiratory fitness	CPET (VO_2_peak)	X			X		X	X
	6-min Walk Test	X	X	X	X	X	X	X
Body composition	bioelectrical impedance analysis, weight, height	X	X	X	X	X	X	X
Physical Activity	Accelerometry	X		X	X	X	X	X
Depression	CES-D	X	X	X	X	X	X	X
Distress	NCCN-Distress	X	X	X	X	X	X	X
Locus of control	KKG (German)	X	X	X	X	X	X	X
Cognitive function	Trail-making-test	X	X	X	X	X	X	X
Common side-effects	VAS, every week, later every 3 weeks							
Biomarker	Various methods (ELISA)	X	X	X	X	X	X	X
Oxidative stress marker	Analysed in urine samples	X	X	X	X	X	X	X
Others								
Socio-demographic factors	Recording of date of birth, education, occupation, familial situation, smoking, alcohol consumption	X					X	X
Medical history	Recording of pre-existing diseases, therapies	X						
Treatment data	Conditioning, complications		X					
Karnofsky Performance Score	Physician rating	X	X	X	X	X	X	X
Medication (immunosuppression, corticosteroids, analgesics)	Recorded at each visit/phone call on a medication log form	X	X	X	X	X	X	X
Physical activity history	Physical activity in adolescence, pre-diagnosis, during, and after intervention is recorded, including walking, cycling, and sports activities	X			X		X	X

### Primary outcome

Two-year overall survival data will be collected using medical logs and will be approved by the study physician (PD).

### Secondary outcomes

#### Non-relapse mortality and median survival

We will distinguish between 2-year non-relapse mortality (e.g. related to GvHD, sepsis), median survival and median disease-free survival. Survival data will be collected using medical logs and will be approved by the study physician (PD).

#### Physical fitness

*Muscle strength* is assessed by measuring isometric (4 positions) and isokinetic (1 angular velocity) maximal muscle capacity with the IsoMed 2000® diagnostic module (isokinetic evaluation and training machine). The protocol includes testing of representative muscle groups for lower (knee extensors and flexors, hip flexor and extensor) and upper (elbow flexor and extensor) extremity. Reliability and validity of isokinetic dynamometer machines have been reported in several studies [36–38]. Additionally, a hand-held-dynamometer (C.I.T. Technics) is applied to assess isometrically 6 different muscle groups within standardized test positions (knee-extensors, knee-flexors, hip-abductors, hip-flexors, elbow-flexors and elbow-extensors) [39]. Each measurement is repeated 3 times, values that are <10 % different from the median will be excluded. Hand-held–dynamometers were already applied in hematological cancer patients [13, 40, 41].

*Endurance performance* (maximum oxygen uptake, VO_2peak_) is measured by performing a symptom-limited maximal cardiopulmonary exercise test (CPET) with a step protocol (starting at 50 watts with steps of 25 watts every 2 min) on a bicycle ergometer. The criteria of exhaustion is defined as achieved estimated maximum heart rate, and respiratory exchange ratio >1.1. VO_2peak_ is defined as highest 30-s average during the test. Peak workload, peak oxygen uptake and oxygen uptake and workload at ventilatory threshold will be taken for analysis. Cardiorespiratory exercise testing is well established in cancer patients and recommendations for testing procedures as well as safety guidelines in clinical trials with cancer populations exist [42–44]. Furthermore, the six-minute walk test is applied to measure submaximal endurance performance. Heat rate and O_2_-saturation is assessed before, during and after the test and the individual perceived exhaustion is measured using the RPE-Scale [45]. For reference values the formula by Enright et al. [46] will be used. The six-minute walk test was already applied in hematological cancer patients [8, 13].

*Body composition* of the participants is estimated with bioelectrical impedance analysis (BIA). This non-invasive method determines the electrical impedance, or opposition to the flow of an electric current through body tissues to calculate an estimate of total body water, fat-free body mass and body fat [47]. BIA gives reliable measurements of body composition with minimal intra- and inter-observed variability [48]. In addition, body weight and height are measured.

*Accelerometer* (ActiGraph GT3X) is used to assess physical activity behavior. The ActiGraph is a triaxial accelerometer, that records motion in different planes and provides information about intensity, frequency and duration of physical activity [49]. Patients will wear the accelerometers during hospital stay for the transplantation and at all measurement points (except t1) for 10 days at home during daytime. Accelerometers were already used in HCT patients [50].

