### Sample size

Sample size was chosen to achieve adequate statistical power (1-β = 0.8) for detecting a difference between the exercise and relaxation group with respect to two-year overall survival (primary outcome). The calculation is based on the two-year overall survival rates of our previous RCT (0.66 in the exercise group vs 0.49 in the control group) [35]. Accordingly, 128 participants per group (total number = 256) are needed to achieve adequate power to detect a significant (two-tailed α = 0.05) difference from Kaplan-Meier estimates tested for equality by log-rank tests.

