### Data analysis

The main intervention effect will be assessed on the basis of a Cox-regression analysis between exercisers and controls (relaxation group) as defined at randomization, regardless of exercise adherence, i.e. according to the intent-to-treat principle.

The differences in secondary endpoints between groups will be assessed using mixed models, which accounts for repeated observations on the same subjects over time. This method provides a more efficient estimate of the intervention effect in pretest-post-test trials than traditional methods [74]. Mixed models will also be used for testing to which extent differences between the treatment groups depend on training adherence, changes in muscle strength, cardiorespiratory fitness, and body composition. Normality assumptions will be checked and, if deviation from normality is detected the data will be transformed accordingly.

In addition, change in physical activity behavior post intervention will be monitored on an explorative basis.

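### As printed, the hand-held-dynamometer cleaning rule is inverted: it discards repeats that agree with the median and keeps only those at least 10% away

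*Protocol article*

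**What the plan says.** The Physical fitness section describes two strength instruments. The first is the IsoMed 2000; Table 1 lists it as "Isometric and isokinetic strength of representative muscle groups for upper and lower extremity measured at the IsoMed2000", measured at t0, t3, t5 and t6. The second is hand-held: "a hand-held-dynamometer (C.I.T. Technics) is applied to assess isometrically 6 different muscle groups within standardized test positions". Table 1 schedules it at every visit from t0 to t6.

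The cleaning rule comes directly after the description of the hand-held device: "Each measurement is repeated 3 times, values that are <10 % different from the median will be excluded". The next sentence is again about hand-held dynamometers, so the rule belongs to that instrument. No other part of the article restates or corrects it.

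Muscle strength is a secondary outcome. The Data analysis section also uses it as an explanatory factor: "Mixed models will also be used for testing to which extent differences between the treatment groups depend on training adherence, changes in muscle strength".

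**The concern.** A consistency check on repeated readings normally removes the discordant ones. The printed rule removes the concordant ones. A reliable test, with three repeats close together, ends with no value. An unreliable test ends with only its outlying readings. The loss is therefore greatest where measurement is best, and what survives is selected for being far from the centre.

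At stake is the hand-held strength outcome: 6 muscle groups × 7 visits = 42 triples of readings for a patient who completes every visit. Of these, 6 × 3 = 18 fall at t1 (discharge), t2 (day 100) and t4 (day 270), where no other strength instrument is scheduled. Any analysis of strength change that draws on the hand-held values would carry the same defect.

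The article states the rule in full: number of repeats, reference value, threshold and action. The problem is a rule stated wrongly, not a detail left to a fuller document.

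**Working it through.** The article gives no figure of its own on this point, so there is none to reproduce. Its one power calculation concerns two-year survival and does not involve this rule.

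**Inputs.** Three repeats, the median as reference and a 10% threshold, all from the Physical fitness section. The within-session CV is not given; it is assumed here and varied from 3% to 15%.

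**Formula.** For repeats x₁, x₂, x₃ with median m, let dᵢ = |xᵢ − m| / m. The printed rule keeps xᵢ only if dᵢ ≥ 0.10. The reversed rule keeps xᵢ if dᵢ ≤ 0.10.

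**Step 1: what follows without any assumption.** With three repeats, m is one of the readings, so its d = 0. The printed rule always drops it and can never keep all three. If every dᵢ < 0.10, it keeps none. The reversed rule always keeps m, so at least one reading remains.

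**Step 2: worked triples (median 100 in each).**

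| Repeats | d | Printed rule keeps | Reversed rule keeps |
|---|---|---|---|
| 100, 104, 97 | 0, 0.04, 0.03 | none | 100, 104, 97 |
| 100, 104, 80 | 0, 0.04, 0.20 | 80 | 100, 104 |
| 100, 112, 98 | 0, 0.12, 0.02 | 112 | 100, 98 |
| 100, 115, 80 | 0, 0.15, 0.20 | 115, 80 | 100 |

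**Step 3: size of the loss.** 400,000 triples were simulated at each CV as x = 100(1 + CV × Z), with Z standard normal. The last two columns give the SD of the session score if the retained readings are averaged. Averaging is a further assumption, and the printed-rule SD covers only triples with something left.

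| Assumed CV | No reading left | One left | Two left | SD, printed rule | SD, reversed rule |
|---|---|---|---|---|---|
| 3% | 99.3% | 0.7% | 0.0% | 8.0 | 1.8 |
| 5% | 86.3% | 13.5% | 0.2% | 9.7 | 3.4 |
| 8% | 56.1% | 39.7% | 4.2% | 11.9 | 5.9 |
| 10% | 41.4% | 49.0% | 9.6% | 13.2 | 7.4 |
| 15% | 21.6% | 53.9% | 24.5% | 16.4 | 10.8 |

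More than half of the tests lose every reading at CVs up to 8%, and fewer than half do at 10% and above. At every CV examined, the scores that survive the printed rule are noisier than those under the reversed rule.

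**The case against.** The strongest reply is that this is a slip of the pen. A rule that deletes its own reference value would empty many records at once and would probably be noticed in data handling. The Background contains what looks like a similar slip: it calls baseline fitness protective against non-relapse mortality and gives a p-value greater than .001. Nothing in the article shows that the rule was programmed as printed. This stands, and it lowers the severity. It does not remove the point, because the printed sentence is the only statement of the rule, and following it gives a wrong result.

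Three stronger readings are tempting, and the article does not support them.

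- A reader might infer that the trial's strength outcome as a whole is lost. It is not. The rule is attached to the hand-held device, and IsoMed2000 strength is measured at baseline (t0), day 180 (t3), day 365 (t5) and day 720 (t6). The planned analysis of strength change names no instrument, so IsoMed2000 change could supply it. The primary endpoint, two-year overall survival from medical logs, is untouched.
- A reader might infer that hand-held data would be mostly missing. That holds only at the lower assumed CVs.
- A reader might assume that the retained readings are to be averaged. The article names no summary, and an article may leave that choice to a fuller document.

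**Conclusion.** The rule is wrong as written. That conclusion rests on the printed words alone and needs no assumed figure: the median and all repeats that agree with it are discarded, and only readings at least 10% away are kept. How much data would be lost does depend on an assumption. With normally distributed repeats, the share of tests left empty runs from about 99% at a CV of 3% to 22% at a CV of 15%.

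The scope is the hand-held-dynamometer outcome, with most consequence at t1, t2 and t4, where it is the sole strength measure. The damage is conditional on the rule being applied literally, and it can be undone if the raw repeats were kept. Severity is moderate.

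**What to change.** In the Physical fitness section, change the less-than sign to a greater-than sign, so that repeats differing from the median of the three by more than 10% are excluded. Check that the derivation code works in this direction. If it was coded as printed, re-derive the hand-held scores from the raw repeats. The sponsor should confirm the intended rule and state which summary of the retained readings (mean, median or maximum) is analysed.

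The cost is one character in the text and a check of the code. No new data are needed.
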